### Sham, randomisation and blinding

The sham intervention will be given through the same coil as the iTBS treatment and both active and sham will be administered over the left DLPFC using neuronavigation coordinates derived from rsfMRI. For the sham group, pulses will be delivered at 30% stimulator output by orienting the coil perpendicular to the scalp surface with direct contact. This will ensure that an appropriate audible noise is created to reinforce the integrity of the treatment blinding.

The study statistician will generate allocation by randomising blocks of participants, ensuring age and sex matching between arms. Block randomisation (block size 6) will be used and determined using online tools (http://www.jerrydallal.com/random/randomize.htm). Initially 30 subjects will be randomised with 3 subjects per group in each block. Given the recruitment rates and feasibility of recruiting all subjects within the time frame, the next subjects will be randomised similarly. However, if recruitment suggests a shortfall of subjects within the time frame the block allocation will be adjusted such that a higher rate of subjects are recruited to the treatment group such as to ensure sufficient numbers in that group. This is expected to be at most a small adjustment such that the block of 6 will still be sufficient to effectively mask assignment, for example, 4 into the treatment group and 2 into the sham group. The study coordinator (BM) will enrol and assign participants.

Study participants will be blinded to the intervention allocation and participants will be asked whether they can guess the type of intervention as part of a TMS exist interview/questionnaire. The study team involved in delivering the intervention cannot be blinded, but the data analysis team will be blinded to which intervention was delivered. Participants will be unblinded if they were to experience adverse events.

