## Methods and analysis

### Trial design

Single centre, sham controlled randomised mechanistic pilot study at the University of Nottingham with a parallel group study design, whereby participants will either receive active iTBS or sham iTBS with random allocation of 2:1. The uneven allocation was chosen to achieve blinding but preferencing power for statistical analyses in the active condition.

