### Sample size

The pilot aims to recruit n=45 (30 active, 15 sham iTBS) participants. In this pilot study, we estimate the variance of the outcome measures, and adjust for the upper confidence level.^27^

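### The 2:1 ratio and the 30:15 arm sizes contradict the block scheme, which gives 21 to 26 active participants out of 45

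*Protocol article*

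**What the plan says.** Three sections of the protocol article bear on allocation.

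- Trial design: "participants will either receive active iTBS or sham iTBS with random allocation of 2:1". The reason given is blinding, with preference for power in the active condition.
- Sample size: "The pilot aims to recruit n=45 (30 active, 15 sham iTBS) participants". It adds that the variance of the outcome measures will be estimated and adjusted for an upper confidence level. It gives no level, width, SD or power.
- Sham, randomisation and blinding: "Block randomisation (block size 6) will be used", and "Initially 30 subjects will be randomised with 3 subjects per group in each block". If recruitment is on course, "the next subjects will be randomised similarly". Otherwise, "if recruitment suggests a shortfall of subjects within the time frame the block allocation will be adjusted" towards the treatment group. On its size: "This is expected to be at most a small adjustment such that the block of 6 will still be sufficient to effectively mask assignment", with the illustration "for example, 4 into the treatment group and 2 into the sham group".

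Trial status reports that 28 participants had completed by March 2023.

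**The concern.** The first two sections agree with each other and describe a 2:1 trial. The third describes a 1:1 trial with an optional late shift. In it, a 2:1 block appears only as an example of a contingency, not as the design. A reader cannot tell from the article how participants were allocated or how large the arms will be.

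Allocation ratio and arm sizes are basic facts of a randomised trial. Two of the four primary outcomes here are variances of change, so arm size sets the confidence limit of any per-arm estimate. If the ratio changes partway, the arms also differ in when their participants were enrolled, and a between-arm analysis has to allow for that.

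**Working it through.** **Inputs.** N = 45, 2:1, 30 active and 15 sham (Trial design; Sample size). Block size 6, first 30 at 3:3, then 3:3 or an adjusted block such as 4:2 (Sham, randomisation and blinding).

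**The plan's own figure.** 45 × 2/3 = 30 active and 45 × 1/3 = 15 sham, so the ratio and the arm sizes agree with each other.

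**The block scheme.** The first 30 make 30/6 = 5 blocks at 3:3, which is 15 active and 15 sham. The last 15 make two full blocks and 3 places of a third. Active total = 15 + 2 × (active per block) + (active among the 3 places).

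| Blocks for the last 15 | Active total | Expected active:sham |
|---|---|---|
| 3:3 | 15 + 6 + (0 to 3) = 21 to 24 | 22.5:22.5 |
| 4:2 | 15 + 8 + (1 to 3) = 24 to 26 | 25:20 |
| 5:1 | 15 + 10 + (2 to 3) = 27 to 28 | 27.5:17.5 |
| 6:0 | 15 + 12 + 3 = 30 | 30:15 |

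Only 6:0 gives 30:15, and that is not random allocation. With 3:3 for 30 participants and 4:2 afterwards, 30 active would need 30 + 15/(4/6) = 52.5, so about 53 participants.

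**The alternative.** With 4:2 from the first participant, seven full blocks give 28:14. The 3 remaining places add 1 to 3 active, for 29 to 31 active and an expected 30:15. This matches Trial design and Sample size.

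**Effect on variance estimates.** Upper one-sided limit of an SD = s × √[(n − 1)/χ²], with χ² the lower (1 − c) quantile on n − 1 df. The article states no confidence level, so c = 80% and 95% are assumed. Multiples of s:

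| Estimate | 80% | 95% |
|---|---|---|
| Active arm, n = 30 | 1.136 | 1.280 |
| Active arm, n = 25 | 1.153 | 1.316 |
| Active arm, n = 22 | 1.166 | 1.346 |
| Sham arm, n = 15 | 1.216 | 1.460 |
| Sham arm, n = 20 | 1.177 | 1.370 |
| Pooled, 43 df, any split | 1.107 | 1.218 |

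The active-arm limit widens by between 1.153/1.136 − 1 = 1.5% and 1.346/1.280 − 1 = 5%. The sham-arm limit narrows and the pooled limit does not change.

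**Effect on the arm comparison.** SE = SD × √(1/n₁ + 1/n₂): 0.316 SD at 30:15, 0.300 SD at 25:20 and 0.298 SD at 22:23.

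**Effect of a change of ratio.** If the two phases are pooled and the outcome drifts by d between them, the bias is d times the difference between arms in the share enrolled in the second phase. For 3:3 then 4:2 this is 10/25 − 5/20 = 0.40 − 0.25 = 0.15, so 0.15d. At an assumed drift of 0.2 SD it is 0.03 SD, a tenth of the 0.30 SD standard error.

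**The case against.** It can be said that the randomisation text already provides for 2:1 blocks and that an article condenses a fuller protocol. Neither answers the point. The 4:2 block is an example for later participants only, and even if used for all of them it stops at 26 active. Nothing is said to be missing either: the article's own sections state incompatible facts.

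The weightier objections limit what follows from the contradiction, and they stand.

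- A reader might infer that the trial's precision or power is wrong. The article states no numerical precision or power, so none can be. The shift is small, and for the arm comparison it is slightly favourable.
- A reader might infer that 1:1 is the true design and 2:1 the error. Two sections agree on 2:1, and 4:2 blocks throughout would deliver it, so the randomisation text may be what is misstated.
- A reader might infer that the reason given for unequal allocation is false because the hypotheses compare with sham. The article claims an advantage in the active condition, and a larger active arm does serve that. It also fits the objective of testing the feasibility and tolerability of active treatment. The cost to the arm comparison is 0.316 against 0.298 SD, about 6%, which is a defensible choice.
- A reader might infer a serious drift bias from assigning the last 15 all to active. The article never proposes that.
- A reader might argue that the shortfall branch means fewer than 45 participants. The adjustment is triggered by a projection, so 45 may still be enrolled.

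**Conclusion.** The contradiction is real, and no other section resolves it. As written, the block scheme gives 21 to 24 active of 45 (about 22:23) if 3:3 continues, or 24 to 26 active with 19 to 21 sham if the last 15 use 4:2. It does not give 30:15. These totals assume that all 45 are randomised and that only the last block is incomplete.

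This is a wrong statement of the allocation ratio and arm sizes on one side or the other, and the article does not show on which. The consequence for precision is modest: about 1.5% to 5% on the active-arm SD limit at the assumed confidence levels, nothing on the pooled limit, and a slight gain for the arm comparison. What is lost, if the block scheme is the operative one, is most or all of the intended preference for the active arm.

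**What to change.** Check the actual allocation list. With 28 completed by March 2023, most of the first 30 had been allocated by then, so the composition of those blocks is known. Then state one ratio, one block composition and matching arm sizes in Trial design, Sample size, and Sham, randomisation and blinding.

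- If 4:2 blocks were used from the start, correct the randomisation text and keep 2:1 and 30:15. Because 45 is not a multiple of 6, the totals may differ by one.
- If the randomisation text was followed, restate the ratio as about 1:1 with 22 to 23 per arm, or as 24 to 26 active and 19 to 21 sham if the last 15 use 4:2.
- If the ratio changes during the trial, state when and by what rule, and include allocation phase as a stratum in the between-arm analyses. The analysis plan is not shown, so this is a condition of changing the ratio and not a claim that the term is missing.

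The cost is wording in three sections, one model term if the ratio changed, and a smaller stated active arm if the block scheme was followed. No extra participants are needed.

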### Objectives

To test the feasibility and tolerability of an optimised accelerated 4-day (over 1 week) iTBS protocol with five daily sessions (total pulses 36 000 aimed at 80% resting motor threshold (RMT)) using connectivity-guided targeting of the left DLPFC in chronic knee OA patients with moderately severe pain.To assess the variance of mechanistic outcome markers comparing the intense iTBS protocol vs sham.To explore clinical efficacy metrics, and the feasibility of online recorded patient-reported outcome measures (PROMs) in the iTBS and sham arm.To explore the effects of iTBS on negative affect, stress and arousal between iTBS and sham.To assess feasibility of blinding using sham TMS.

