### Transcranial magnetic stimulation

TMS will be delivered using the Magstim Horizon Performance system with StimGuide Navigated TMS package (The Magstim Co Ltd). Single-pulse TMS will be applied to the left motor cortex using a handheld figure-of-eight coil (diameter 7 cm) to determine the RMT. RMT is defined as the minimum stimulator output intensity needed to achieve a minimum motor evoked potential-amplitude of 50 μV in the completely relaxed abductor pollicis brevis-muscle in at least 5 out of 10 trials. For all treatments, the iTBS protocol will be delivered using a fixed 7 cm diameter coil (E-z Cool Coil and support arm) consisting of three pulses (aimed at 80% RMT, but may be lowered to avoid participant discomfort) of 50 Hz repeated at 200 ms (5 Hz) intervals with a total 1800 pulses per block, 9000 pulses per visit/day and 36 000 pulses in total/treatment week.

The staff operating the TMS device (SZ, senior research nurse with 3 years experience in rTMS treatment/trials; DH senior research fellow with 2 years experience in research TMS) are trained on the MAGSTIM system and adhere to all safety instructions.

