#### Secondary

Variance of change in reported pain intensity, burden and catastrophising at final versus baseline study visit (ICOAP, PCS).Change in negative affect (HADS) at final versus baseline study visit.Variance in physiological and psychophysical changes (acute experimental pain) at final versus baseline study visit.Variance of PROMs (daily online recording pain, well-being, sleep) over 16 weeks from treatment versus enrolment-baseline.

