### Known side effects and discomfort

The staff operating the TMS device (SH 3 years, DH 2 years) are trained and adhere to all safety instructions.

As it directly influences activity of nerve cells, theoretically there is the risk of a seizure although the risk level is considered low. The cumulative number of TMS pulses is 36 000 which is substantially lower than the accelerated Stanford protocol and lower than the FDA approved protocol (48 000–72 000 for 4–6 weeks).

Staff and participants will be wearing ear protectors because of the risk of tinnitus and hearing impairment from the loudness of the TMS.

The majority of TMS treatments are very well tolerated, occasionally however a short-lasting headache can occur. Depending on an individual’s facial anatomy, facial nerves can be stimulated at the same time which would result in muscle twitches in the face; these however cease as the stimulation is stopped.

Should a participant experience any side effects and find it too uncomfortable, the treatment session can be stopped immediately but where possible, adjustments will be made to ease discomfort. To reduce participants' discomfort on the first day of the session, the power was individually ramped to 80% RMT or lower depending on subjective tolerability.

A standard operating procedure has been developed that defines the discontinuation of the trial intervention, referral to treatment as required and risk management of the most common serious side effect (seizure) and more common side effects like headache and dizziness.

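### Unblinding participants on any adverse event is too broad as printed: it can contaminate the blinding estimate and bias the exploratory comparisons with sham

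*Protocol article*

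**What the plan says.** The rule is one sentence in Sham, randomisation and blinding: "Participants will be unblinded if they were to experience adverse events". Nothing elsewhere in the article narrows it by seriousness, relatedness or need to know.

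Four other parts of the article bear on it:

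- **Expected effects.** Known side effects and discomfort says that "occasionally however a short-lasting headache can occur", describes facial muscle twitching that stops with the stimulation, and refers to an operating procedure covering seizure and "more common side effects like headache and dizziness".
- **Blinding as an aim.** The last objective is "To assess feasibility of blinding using sham TMS". The only check described is that "participants will be asked whether they can guess the type of intervention as part of a TMS exist interview/questionnaire". Its timing relative to any disclosure is not given.
- **What is measured afterwards.** Visit 6 falls 18-72 hours after the last session (Study procedures). It includes conditioned pain modulation (CPM), whose change is a primary outcome, and the ICOAP, PCS and HADS questionnaires. Self-reports then run on, with the secondary outcome "Variance of PROMs (daily online recording pain, well-being, sleep) over 16 weeks from treatment versus enrolment-baseline".
- **The two arms.** Active pulses are "aimed at 80% RMT, but may be lowered to avoid participant discomfort". For sham, "pulses will be delivered at 30% stimulator output by orienting the coil perpendicular to the scalp surface with direct contact".

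The delivery team is unblinded, and the analysis team is blinded.

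**The concern.** Read literally, any recorded adverse event leads to the participant being told the allocation. The effects that the article itself expects are mostly minor and would arise around the treatment sessions. Disclosure could therefore come before visit 6, before almost all of the self-report period and before the exit question.

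Two things are at stake.

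1. **The blinding estimate.** A participant who has been told is no longer guessing. If such answers are pooled with the others, the share of correct guesses rises even when the sham is fully convincing. The article names uncertain blinding as a limitation of earlier work, so this result matters for the later trial that the pilot is meant to guide.
2. **Comparisons with sham.** Pain ratings, catastrophising, mood and pressure pain thresholds depend on the participant's own response and can move with expectation. One of the staff who operate the stimulator also performs all the sensory testing, and the delivery team knows the allocation. Participant blinding is therefore the main protection left for CPM.

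**Working it through.** **Inputs from the article.** Planned numbers are 30 active and 15 sham (Sample size). There are no adverse event rates, overall or by arm, and no expectation effect. Safety assessment reports only that the first 10 participants had no serious side effects. There is thus no stated figure to reproduce, and every rate and effect below is an assumption.

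**Step 1. Number told.** Expected number = n × p in each arm.

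| Assumed rate, active / sham | Active told | Sham told | Share of 45 not told |
|---|---|---|---|
| 5% / 5% | 1.5 | 0.75 | 95% |
| 10% / 5% | 3.0 | 0.75 | 92% |
| 30% / 10% | 9.0 | 1.5 | 77% |
| 50% / 20% | 15.0 | 3.0 | 60% |

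Even at 5%, the chance that at least one active participant is told is 1 − 0.95^30 = 0.785. At 10% it is 1 − 0.90^30 = 0.958.

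**Step 2. Blinding estimate.** Suppose that disclosure precedes the question, that told participants answer correctly, and that everyone else guesses at 50%. Expected correct = p + 0.5(1 − p) = 0.5 + 0.5p. This gives 52.5% at p = 5%, 55% at 10%, 65% at 30% and 75% at 50%, although blinding is perfect in everyone not told.

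**Step 3. Bias in a between-arm mean.** Suppose that knowing one is on active lowers reported pain by e, and knowing one is on sham raises it by e. Bias = e × (pA + pS), on the 0-10 scale:

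- low end: 0.5 × (0.20 + 0.10) = 0.15 points;
- middle: 1 × (0.30 + 0.10) = 0.40 points;
- high end: 1 × (0.40 + 0.15) = 0.55 points.

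The formula uses the sum of the rates, not their difference. Equal rates of 20% and 20% with e = 1 also give 0.40.

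In SD units, with e = 0.3 to 0.5 SD, the bias is 0.03-0.05 SD at 5%/5%, 0.12-0.20 at 30%/10%, 0.18-0.30 at 30%/30% and 0.21-0.35 at 50%/20%. For scale, the standard error of the mean difference is √(1/30 + 1/15) = 0.316 SD.

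**Step 4. Effect on variances.** Most outcomes are worded as variances of change. Mixing told and untold participants within an arm inflates the variance by 1 + p(1 − p)e², with e in SD. This runs from 1.004 (p = 5%, e = 0.3) to 1.0625 (p = 50%, e = 0.5), which is small.

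**The case against.** The strongest reply is that the sentence is a condensed line in a journal article. The term adverse events occurs only there, whereas headache, dizziness and twitching are called side effects or discomfort and are handled by adjusting or stopping the session. The operating procedure is not shown and may hold a narrower rule. This is fair, and it means that disclosure for a mild headache is a reading of the text, not something the article reports. But the sentence is a positive, unqualified instruction, and nothing printed restricts it, so clarification is still needed.

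The second reply is that this is a pilot which mainly estimates variances, with efficacy exploratory. That also stands: Step 4 shows little effect on the variances. The harm falls on the blinding objective and on the comparisons with sham that the hypotheses name.

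A reader might go further and infer three things that the documents do not support:

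- *The blinding check is void.* Only answers given after disclosure are affected. In the scenarios above, 60-95% of participants remain usable, and nothing says that told participants would be counted as correct guesses.
- *Disclosure is known to fall mainly on active.* More events on active is plausible, given the difference in stimulation between the arms. No rates by arm are given, and the bias does not need such an excess.
- *Disclosure is known to occur in the treatment week and before the exit question.* The article states neither the timing of disclosure nor its order relative to that question.

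**Conclusion.** The concern holds as a defect in a stated rule. As printed, the rule works against the blinding that the trial sets out to test. It can contaminate the estimate of blinding and can bias the exploratory between-arm comparisons of self-reported and sensory-testing outcomes.

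The size is unknown. The 0.15-0.55 point range rests entirely on the assumed event rates and on an assumed expectation effect acting in opposite directions in the two arms. At event rates near 5% both effects are slight. At 30% or more on active, the correct-guess rate in that arm would be 65% or higher without any failure of the sham. The bias in mean differences would stay below one standard error in a trial of this size in most of the scenarios, but a larger trial run under the same rule would not average it away.

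The primary imaging, recruitment and session-count outcomes give no comparable cause for concern on this ground.

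**What to change.** 1. Reconcile the sentence with Known side effects and discomfort and with the blinding objective, so that an adverse event does not by itself automatically disclose allocation to the participant. Which events warrant disclosure is for the sponsor and the medical safety advisor to set; this review proposes no criterion. The delivery team already knows the allocation, so staff need not tell the participant in order to know it themselves.
2. Log the date, reason and recipient of every disclosure.
3. Obtain the allocation guess before any disclosure.
4. Report guesses by arm, with participants already unblinded when asked shown separately.
5. Add sensitivity analyses of the patient-reported outcomes and of CPM and other sensory testing without unblinded participants. These should support, not replace, the analysis of everyone randomised, because leaving out people who had events can itself make the arms less comparable.

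The cost is small: a revised sentence, one log and a little more analysis. By March 2023, 28 participants had completed (Trial status), leaving 45 − 28 = 17 of the planned number. The change in guess timing can apply only to those not yet completed. If past disclosures were recorded, items 4 and 5 can cover the earlier participants too.

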### Assessments

Data will be collected for the following

MRI at visit 1 and at visit 6 (pretreatment and post-treatment).QST at visit 1 and at visit 6 (pretreatment and post-treatment).

REDCap (https://www.project-redcap.org/) will be used to administer online questionnaires:

Pain characteristics

A numerical pain VAS (0–10) as online daily pain report.Weekly questionnaires:Intermittent and Constant Pain Score (ICOAP),^18^ the Central Aspects of Pain in the Knee (CAP-Knee) questionnaire.^19^At visit 1 and 6:painDETECT,^20^ Pain Catastrophizing Scale (PCS),^21^ ICOAP,^18^ General Anxiety Depression scale (GAD-7),^22^ Depression Anxiety Stress Scales (DASS-21),^23^ Hospital Anxiety and Depression Rating-Scale (HADS),^24^ Patient Health Questionnaire (PHQ-9),^25^ CAP-Knee,^19^ Montreal Cognitive Assessment test.^26^

